#### Phase 1: Prototype

In phase 1, data collection will take place through a customized Labfront smartphone app installed on participants’ smartphones and connected via Bluetooth to a Garmin VivoActive 5 worn by participants (as outlined in Figure 1). Quantitative data captured passively through the Garmin wearable as well as compound measures, such as stress level and sleep score (Table 1), will be securely transmitted to the encrypted Labfront cloud by Garmin’s Health application programming interface. The use of Garmin’s application programming interface enables access to the raw data from the smartwatch. All participant data are anonymized before entering the Labfront system.

The EMA surveys that participants will receive in the Labfront app have been developed for participants to record data on seizures (timing, duration, type, and severity), seizure precipitants (triggers), prodromal symptoms, and postictal symptoms. EMA survey completion will be prompted twice daily by notification to the participant at a set morning and evening time. An optional menstrual cycle set-up survey may be completed at the start of participation. Completed surveys will be uploaded to the secure Labfront cloud, where they can be accessed by permissioned members of the core research team.

**Figure 1 figure1:**
[figure not shown]
An overview of the phase 1 interactive prototype. API: application programming interface.

#### Phase 2: MVP

The design and development of the MVP were informed by earlier co-design and usability studies [18]. The anticipated development plan includes the creation of a custom-built smartphone app for phase 2, which will be developed using Swift, Apple’s native programming language for iOS. An agile software development methodology will be used, encompassing several iterative development and feedback cycles with stakeholders. Operating under a licensing agreement, the app will use the Garmin Health Standard Software Development Kit, which enables health and fitness data, such as heart rate and sleep, to be transferred from Garmin wearable devices to the app. Data being collected via the MVP are defined in Table 1. Quantitative data from the connected Garmin Vivoactive 5/6 device will be passively sent to the MVP app installed on an Apple iPhone. This will be relayed to an encrypted cloud database hosted in a secure digital environment in Amazon Web Services (AWS), independent of Garmin’s own services or databases. User self-reported data relating to EMA data defined in Table 1 will be similarly relayed to the same encrypted cloud database. Authentication to upload and download data from this database will be managed through AWS Cognito, which adopts the industry standard OAuth 2.0 protocol.

#### Algorithm Development

As part of this project, we are developing a seizure forecasting algorithm that uses physiological time series data collected from a smartwatch. The algorithm calculates time- and frequency-domain feature statistics, which are combined with seizure timings, obtained from the companion app to train and test a combination of machine learning models to extract seizure propensity scores in different time scales. The data collected via the data collection technology will be added to the existing ATMOSPHERE dataset and used to refine and advance the seizure forecasting algorithm.

### Study Procedures

Study procedures are illustrated in the template study flow diagram in Figure 2.

**Figure 2 figure2:**
[figure not shown]
Study flow diagram showing participant flow through the study. Recruitment phases in pink and yellow, retention phases in blue and green, and a qualitative interview for a subgroup of participants in purple. CROM: clinician-reported outcome measure; PROM: patient-reported outcome measure.

#### Procedure 1: Deployment of Prototypes

A pack containing a smartwatch and instructions for using the smartwatch and companion app will be sent to participants. An onboarding session will be held online with each participant to support the setup of the prototype. Participants will be invited to use the technology for up to 6 months. Each participant’s data will be reviewed monthly, and continuation of technology use for the following month will be contingent upon the participant wearing the smartwatch for some time and responding to the app questions on at least 21 days during the current month.

During the prototype deployment, incoming data will be monitored by the research team through dashboards generated within the Labfront software. Each week, participants will be sent an email summarizing their engagement with the prototype, including device wear time and survey completion. If missing data are noted, such as a survey completion rate falling below 80%, an in-app notification will be sent to participants reminding them to respond. If issues persist, follow-up via email will be conducted by the research team to offer troubleshooting support.

During the MVP deployment phase, incoming data will be monitored, and, if issues with use are identified, the MVP will be refined accordingly.

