#### Inclusion or Exclusion Criteria

Adults (aged 18 years and older) will be eligible for inclusion if they have a diagnosis of epilepsy; are likely to have a seizure at least twice per month (seizure data required for modeling); are fluent in English (to be able to engage with the technology and qualitative interview); can provide informed consent; have access to an email address; can wear a wrist wearable device (smartwatch), supplied as part of the study; can input data into a smartphone app; own a smartphone that can download apps from either the Apple Store or the Google Play Store (for phase 1); and own an iPhone that can download apps from the Apple Store (for phase 2).

Adults will be excluded if they have a major cardiac condition, have a diagnosis of a major psychiatric condition (defined as needing secondary care mental health services support), and have a diagnosis of functional dissociative seizures or reflex epilepsy.

The aim is to screen all participants attending the clinics, with all participants who are eligible being given initial information and invited to consent to be contacted. All participants who consent to contact will be offered a meeting with a researcher and an opportunity to consent to the study. This is to reduce bias in the study. Where possible, reasons for nonscreening, nonconsent to contact, and nonconsent will be recorded, so that recruitment processes can be monitored.

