Objective 1 includes exploring the rate of recruitment and the diversity of the sample recruited. This will be used to inform a fully powered trial, for example, guiding the selection of additional sites and the length of the trial. This feasibility study will be used to determine the time frame needed to recruit 60 participants and the diversity of this sample. A sample size of 60 was selected to meet the requirements of objectives 2 and 3 (see below) and aligned with the typical sample size and recommendations for feasibility studies [31,32].Objective 2 focuses on refining the data collection technology of the seizure forecasting system. To do this, purposeful sampling will be used to identify 9-12 participants to invite them to take part in qualitative interviews to explore their experiences of using the MVP of the technology and identify any usability issues. Sampling for diversity will take place, with a focus on including individuals with lower digital literacy and from lower socioeconomic status groups. This is to ensure that the data collection technology is designed to include the needs of these groups to reduce the risks of digital exclusion and exacerbations of health inequalities. A sample size of 9-12 is considered sufficient to identify most usability issues in qualitative usability testing [33], ensuring a rich understanding of user experience and potential areas for improvement.Objective 3 seeks to add the data collected to the existing dataset to support the optimization of the seizure forecasting system. As the forecasting will be personalized and the system will be tailored to individual participants, the focus will be on obtaining accurate and continuous longitudinal data from each participant.

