### The Data Collection Technology

#### Overview

The technology for collecting real-time data underpinning the seizure forecasting system consists of a smartwatch and a companion smartphone app referred to as the data collection technology. Previous iterations of the smartphone app prototype have undergone co-design and usability testing [18]. In this study, participants will be given either version 1 (the prototype) or version 2 (the MVP) of the technology, depending on their point of entry into the study. The primary difference between the prototype and MVP is that the prototype uses a third-party app (Labfront) integrated with the smartwatch, whereas the MVP will be a novel smartphone app developed by the research team. Both versions will collect the same data points, as outlined in Table 1.

**Table 1 table1:** Data collection protocol.

Data point		Labfront data collection schedule	MVP^a^ data collection schedule

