**User-initiated^c^ data via smartphone app (EMA^d^)**			
	Seizure event (type, timing, duration, severity)	Twice daily notification^e^	A twice daily notification and ad hoc user-initiated
	Prodromal symptoms	Twice daily (notification)	Twice daily notification and ad hoc user-initiated
	Postictal symptoms	Up to twice daily (notification; optional if seizure event reported)	As required (if seizure event reported)
	Epilepsy medication use: routine medication	Once daily (notification)	Customized notification and ad hoc user-initiated
	Epilepsy medication use: emergency medication	Once daily (notification)	As required, ad hoc user-initiated
	Emotional states and emotional intensity	Twice daily (notification)	Twice daily (notification) and ad hoc user-initiated
	Sleep duration and quality	Once daily (notification)	Once daily (notification)
	Acute illness or infection	Twice daily (notification)	Twice daily notification and ad hoc user-initiated
	Menstrual cycle	One off series of questions (optional)	One off series of questions (optional), which can be updated
	Alcohol	N/A^f^	Ad hoc user-initiated
	Personalized trigger	N/A	Ad hoc user-initiated

^a^MVP: minimum viable product.

^b^Compound measures through the Garmin application programming interface.

^c^User-initiated: users can complete the EMA item any time within the app.

^d^EMA: ecological momentary assessment.

^e^Notification: smartphone notification to prompt the user to complete the EMA item.

^f^N/A: not available.

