#### Objective 2: Feasibility Outcomes Measures and Analysis: Refining the Intervention

##### Outcome 6: Usability

###### Quantitative Use Metrics

Usability will be assessed through descriptive statistics of wear time (assessed using the presence of heart rate data), proportion of participants who complete the scheduled questionnaires at each time point. These quantitative indicators will offer insight into the feasibility and acceptability of both the data collection technology and associated data collection procedures.

To determine feasibility to progress to a larger study and full trial, we will consider the study feasible if at least 80% (≥48/60) of participants achieve an average wear time of ≥19 hours per day across the study period and a total average score of 5 on the MAUQ. This threshold was informed by established usability benchmarks for the System Usability Scale, which has been shown to be strongly correlated with the MAUQ [42].

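### Wear-time and retention progression thresholds are read on 60 participants pooled over two app versions with an unstated split, so they can be met while the MVP misses them

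*Protocol article*

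**What the plan says.** The Sample Size section sets one sample for both versions: "This feasibility study will be used to determine the time frame needed to recruit 60 participants and the diversity of this sample". Under The Data Collection Technology (Overview), each participant gets the prototype or the MVP according to when they enter. No number per version is given.

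The progression criteria do not separate the versions:
- Wear time (Outcome 6, Quantitative Use Metrics): "at least 80% (≥48/60) of participants achieve an average wear time of ≥19 hours per day across the study period", joined by 'and' to an average MAUQ score of 5.
- Retention (Outcome 4): 80% at follow-up, with deployment counted over either version.
- Recruitment (Outcome 1): at least 70% of the single target.

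The versions differ in three ways:
- Phone: phase 1 accepts phones using either app store; phase 2 requires an iPhone (Inclusion or Exclusion Criteria).
- Software: a third-party app in phase 1, a new in-house iOS app in phase 2.
- Described support (Procedure 1): for the prototype, "Each week, participants will be sent an email summarizing their engagement with the prototype, including device wear time and survey completion", plus an in-app reminder when survey completion drops below 80% and email troubleshooting if problems persist. For the MVP: "During the MVP deployment phase, incoming data will be monitored, and, if issues with use are identified, the MVP will be refined accordingly".

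On content, the Overview states: "Both versions will collect the same data points, as outlined in Table 1". Table 1 lists alcohol and personalized trigger as N/A for Labfront and as collected by the MVP.

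**The concern.** A refined MVP is the stated product of objective 2 (Principal Findings). The question for progression is therefore whether people with epilepsy keep wearing the watch and stay in the study when using the MVP. A proportion pooled with users of a different app, who are sent weekly feedback on the very quantity being judged, answers a different question. If phase 1 does well, it can supply most of the 48 successes and the MVP can fall well short without the criterion showing it.

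Recruitment and diversity are affected to a lesser degree. A single yield and a single demographic profile average over a period with the iPhone condition and a period without it, and the recruitment estimates are meant to inform timelines and site numbers for the full trial (Strengths and Limitations).

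**Working it through.** **The plan's own figure.** 0.80 x 60 = 48, which reproduces the stated threshold. For recruitment, 0.70 x 60 = 42. The article gives no power calculation to check.

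**Inputs.** The threshold of 48 and the total of 60 come from the article. The split and the success rates are not given and are assumptions here. The only floor on phase 2 that the article implies is the 9-12 interviewees, who must be MVP users.

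**What the MVP must achieve.** MVP successes needed = 48 minus phase 1 successes. Phase 1 at 90% is rounded to whole people: 40 of 45 for 40.5, and 14 of 15 for 13.5.

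| Phase 1 : MVP | Phase 1 successes at about 90% | MVP needs | MVP needs if phase 1 is at 100% |
|---|---|---|---|
| 30:30 | 27 | 21/30 (70%) | 18/30 (60%) |
| 40:20 | 36 | 12/20 (60%) | 8/20 (40%) |
| 45:15 | 40 | 8/15 (53%) | 3/15 (20%) |
| 15:45 | 14 | 34/45 (76%) | 33/45 (73%) |

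For example, 36/40 + 12/20 = 48/60. At the extreme of 48:12 with phase 1 at 100%, the pooled rule is met with 0/12 on the MVP. The same arithmetic applies to retention if its 80% is taken over 60.

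**Chance of passing.** With X1 ~ Bin(n1, 0.90) in phase 1 and X2 ~ Bin(n2, p2) on the MVP, the pooled rule passes with probability P(X1 + X2 >= 48). A rule on MVP users alone passes with probability P(X2 >= 0.8 n2), that is 24/30, 16/20, 12/15 or 36/45.

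| Split | p2 = 60%: pooled | p2 = 60%: MVP alone | p2 = 70%: pooled | p2 = 70%: MVP alone |
|---|---|---|---|---|
| 30:30 | 22% | 2% | 58% | 16% |
| 40:20 | 58% | 5% | 82% | 24% |
| 45:15 | 77% | 9% | 90% | 30% |
| 15:45 | 2% | 0.4% | 23% | 9% |

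**The MAUQ clause.** Only phase 2 completes the MAUQ (Procedure 3). If the rule means 48 of 60 on wear time and, separately, a mean MAUQ of 5, the tables above apply. If each of the 48 must meet both conditions, phase 1 users can never count, and the rule cannot be met unless at least 48 people are in phase 2. In the 40:20 example it would then yield at most 12. On either reading the two conditions need different denominators.

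**Data items.** The Overview sentence and Table 1 cannot both stand for alcohol and personalized trigger. For seizure events, the MVP column reads "A twice daily notification and ad hoc user-initiated", while the Labfront column lists the twice-daily notification alone. Yet footnote c says that user-initiated items can be completed at any time. Whether phase 1 allows ad hoc seizure entry is therefore unclear.

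**The case against.** Much of the evidence on the MVP is not pooled. The MAUQ, the interviews with their acceptability condition, and the technical and safety reports are all phase 2 only. A reader might infer that phase 1 could hide a failing MVP altogether. The article does not support that, because poor perceived usability would still be seen. This part of the objection stands and confines the masking mainly to wear time and retention.

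The thresholds are also not mechanical. A shortfall in recruitment or retention is decisive only if qualitative data suggest that no improvement is possible. The final system will have further user testing before the full trial (Strengths and Limitations). This softens the consequence, but a false pass on the pooled figure would not prompt that scrutiny.

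The support contrast rests partly on silence. MVP data are monitored, and neither the onboarding session nor the monthly 21-day review is restricted to phase 1. The watch is nearly the same in both phases, and the heart-rate stream used for wear time is listed for both. So the difference in wear time may be small. Nothing in the plan ensures that it is.

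Two further inferences should be resisted. One is that the pooled recruitment rate overstates the full-trial rate by some definite factor. The criterion is a count against a target, the article gives neither iPhone ownership nor phase lengths, and nothing says that the full trial will be iPhone-only. The other is that phase 1 seizure times are wrong by up to the gap between prompts. Both versions ask for the timing of the seizure, and footnote c allows entry at any time.

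Reporting by phase could be left to an analysis plan. The 48/60 denominator, however, is fixed in this article.

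**Conclusion.** The point holds for wear time and retention, and more weakly for recruitment and diversity. As written, both thresholds can be met while the version carried forward misses them. How far depends on the unstated split and on phase 1 success. With phase 1 at about 90%, the MVP could pass at 53-70% for splits from 45:15 to 30:30, but would need 76% at 15:45. For wear time this assumes that the 48/60 count and the MAUQ mean are separate conditions. If each participant must meet both, the masking is limited to retention, recruitment and diversity, and the wear-time rule has a different defect. The conflict between the same-data statement and Table 1 stands regardless, but it does not itself bias wear time. The change should be made; it is not a reason to halt the study.

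**What to change.** 1. State the planned number of participants per phase.
2. Report the flow diagram and outcomes 1-6 by phase, where collected.
3. Judge the wear-time and retention thresholds on MVP users with their own denominator, with phase 1 as supporting data.
4. Apply the MAUQ threshold to phase 2 only, and word it as a condition separate from the wear-time count.
5. Add a screening-log entry for patients who are otherwise eligible but have no iPhone, so that recruitment can be projected with and without that restriction.
6. Correct the same-data sentence to match Table 1, say whether ad hoc seizure entry is available in phase 1, and carry an app-version flag in the dataset passed to the modeling team.

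The cost is wording, one log field, stratified tables and less precision. Exact 95% CIs at the threshold are about 61-92% for 24/30, 56-94% for 16/20 and 52-96% for 12/15, against 68-89% for 48/60. An MVP whose true rate is exactly 80% would pass its own threshold only about 61-65% of the time at these three sizes, so the result should be read with its interval and the qualitative evidence.

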#### Procedure 2: Patient-Reported Outcome Measures and Clinician-Reported Outcome Measures

The following demographic and clinical information will be collected about participants at baseline by the clinical team based at the recruiting site. This will be taken from the clinical notes where possible, with additional data collected from the participant if it is not available in the notes: ethnicity, age, highest level of education completed, total annual household income, seizure type, and epilepsy medications and treatments.

Currently, there are no internationally accepted core outcomes for epilepsy, although one is under development [34]. The International Consortium for Health Outcomes Measurement (ICHOM) formed a global working group, including clinicians, people with epilepsy, and advocates, to define a standardized minimum set of outcomes for clinical practice [35]. The clinician-reported outcome measures (CROMs) and patient-reported outcome measures (PROMs) in this study capture these essential outcomes, including seizure- and non–seizure-related outcomes.

Participants will be asked to complete a series of PROMs at baseline and at 3 months. These include Patient-Reported Outcomes Measurement Information System (PROMIS) Cognitive Function Short Form [36], Patient Health Questionnaire (PHQ)-9 [37], Generalized Anxiety Disorder (GAD)-2 [38], PROMIS Sleep Disturbance—Short Form [39], and Quality Of Life in Epilepsy (QOLIE)-10 [40]. Participants will also be asked to complete a digital literacy scale, the Mobile Device Proficiency Questionnaire-16 [41], at baseline only.

A member of the clinical team will also complete a series of CROMs at baseline and at 3 months. These include: mortality; seizure frequency, seizure freedom, emergence of new seizure type, and seizure severity; emergency and unplanned health care services use; seizure control during pregnancy, pregnancy, and delivery complications; and memory.

Participants will have up to 1 month to complete the measures. These can be done either online or in paper format. An email reminder will be sent within the first 2 weeks after the expected completion date. If the measures remain incomplete after 2 weeks, a member of the research team will follow up by phone to assist with completion. Participants may be contacted by phone up to 3 times.

#### Procedure 3: Qualitative Interview and Usability Questionnaire (Phase 2 Only)

At the end of the technology deployment, participants who used version 2 of the prototype (MVP) will be invited to participate in a qualitative interview with a member of the research team. These interviews will be scheduled for up to 60 minutes and use a semistructured topic guide (Multimedia Appendix 3) designed to explore participants’ views and experiences of using the technology.

Participants will also be asked to complete the mHealth App Usability Questionnaire (MAUQ), an 18-item questionnaire, which consists of 3 subscales that focus on ease of use (5 items), interface and satisfaction (7 items), and usefulness (6 items), rated on a 7-point Likert scale (1=strongly disagree to 7=strongly agree) [42].

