###### Stakeholder Consultations

If issues are identified during the recruitment phase, we will engage with people with epilepsy and the key members of the clinical and research teams to identify and document any barriers or problems related to recruitment. In response, practical, context-specific solutions aimed at improving recruitment processes will be developed and implemented collaboratively with the clinical team. This iterative approach will ensure that emerging challenges are addressed promptly and that recruitment strategies remain acceptable and feasible within the clinical setting. A full trial is unlikely to be feasible if we do not reach 70% of our recruitment target, and the qualitative data suggest that recruitment cannot be improved any further.

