##### Outcome 5: Barriers and Facilitators to Retention, With a Focus on Inclusive Trial Design for Those Underrepresented in Health Research

The number and demographics of participants who leave the study, along with reasons for leaving (where known), will also be reported. If issues are identified during the retention phase, we will conduct PPI sessions with people with epilepsy to identify possible solutions to any barriers. A full trial is unlikely to be feasible if retention is <80%, and the qualitative data suggest that retention cannot be improved any further.

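### The MAUQ and interviews come at the end of MVP deployment with no stated offer to early stoppers, so the MAUQ mean and acceptability themes are likely to over-represent those who stayed

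*Protocol article*

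**What the plan says.** All references are to the protocol article.

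- **Timing and population.** Procedure 3, headed as phase 2 only, states: "At the end of the technology deployment, participants who used version 2 of the prototype (MVP) will be invited to participate in a qualitative interview". The interview is "designed to explore participants’ views and experiences of using the technology".
- **MAUQ.** The same procedure continues: "Participants will also be asked to complete the mHealth App Usability Questionnaire (MAUQ), an 18-item questionnaire". No separate time point is given.
- **Length of use.** Procedure 1 says: "Participants will be invited to use the technology for up to 6 months". Each participant is reviewed monthly. Continuing depends on some watch wear and on "responding to the app questions on at least 21 days during the current month".
- **Choice of interviewees.** Sample Size plans 9-12 interviews: "Sampling for diversity will take place, with a focus on including individuals with lower digital literacy and from lower socioeconomic status groups". Early stopping is not a sampling characteristic.
- **Use in decisions.** Outcome 6 makes a MAUQ average of 5 part of the progression criterion, alongside at least 48 of 60 participants averaging 19 hours of wear per day. It also says that a full trial is unlikely to be feasible if users do not find the technology acceptable.
- **Recruitment and retention judgements.** Stakeholder Consultations, under Outcome 3, has a rule that begins: "A full trial is unlikely to be feasible if we do not reach 70% of our recruitment target, and the qualitative data suggest". Its closing words ask for a finding that no further gain in recruitment is possible. Outcome 5 says: "A full trial is unlikely to be feasible if retention is <80%, and the qualitative data suggest that retention cannot be improved any further".

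**The concern.** People who find an app or watch hard to live with are the ones most likely to withdraw, or to fall below the monthly engagement level and be stopped. They can tell the team most about what to repair. If the questionnaire and interview reach only those still using the MVP at the end, the MAUQ mean is measured in a favourable subset and compared with a fixed threshold of 5. The acceptability themes have the same tilt. The team could then take forward a technology that looks usable because those who disagreed were not asked. Once a person has left, this information is hard to recover.

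A related, smaller matter is that the recruitment and retention judgements depend partly on qualitative data. The protocol does not say that people who declined or left will be heard in the consultations that supply those data.

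**Working it through.** **1. The plan's own figure.** Outcome 6 gives 80% of 60 as 48, and 0.80 × 60 = 48, so it reproduces. The point concerns timing and selection, so no power or sample size formula applies.

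**2. Which usability data can miss an early stopper.**

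| Source | Where stated | Tied to the end of deployment? |
|---|---|---|
| Interview, MVP users | Procedure 3 | Yes, as worded |
| MAUQ, MVP users | Procedure 3 | Same procedure, no other time point |
| Wear time, questionnaire completion | Outcome 6 | No |
| In-app issue reports, phase 2 | Aims and Objectives; Outcomes 7 and 8 | No, made in real time |

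Only the first two rows are exposed. No interview or MAUQ at withdrawal, or after a monthly-review stop, is described.

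**3. Size of the effect on the MAUQ mean.** Let r be the share of MVP users who stay, S the stayers' mean and L the mean that leavers would have given.

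- All-user mean = r × S + (1 − r) × L
- Overstatement = S − all-user mean = (1 − r) × (S − L)

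Inputs: r = 0.80 is the retention expectation in Outcome 4. The gap S − L is not in the documents; 1 to 2.5 points on the 7-point scale is an assumption.

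| Retention r | Gap 1.0 | Gap 2.5 |
|---|---|---|
| 0.90 | 0.10 × 1.0 = 0.10 | 0.10 × 2.5 = 0.25 |
| 0.80 | 0.20 × 1.0 = 0.20 | 0.20 × 2.5 = 0.50 |
| 0.70 | 0.30 × 1.0 = 0.30 | 0.30 × 2.5 = 0.75 |

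At 80% retention, a stayers' mean of exactly 5.0 corresponds to an all-user mean of 5.0 − 0.2 = 4.8 down to 5.0 − 0.5 = 4.5. For the all-user mean to reach 5, stayers would have to average 5.2 to 5.5.

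The 80% refers to retention at follow-up, and the outcome measures are collected at 3 months, whereas use runs for up to 6. The share still using the MVP at the end could therefore differ, which is why 70% and 90% are shown.

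**4. Number of people involved.** The number of MVP users is not stated. For an assumed 20 to 40, 80% retention means that 0.20 × 20 = 4 to 0.20 × 40 = 8 people leave. A few of the 9-12 interviews could cover a useful part of that group.

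**5. Qualitative input to the recruitment and retention judgements.** Each judgement comes after a consultation step in its own section: people with epilepsy and the clinical and research teams for recruitment, and Patient and Public Involvement (PPI) sessions with people with epilepsy for retention. Neither section says that people who declined or left take part, and neither excludes them. Reasons for nonconsent and for leaving are recorded where possible or known, but their role in the judgement is not stated.

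**The case against.** The strongest reply is that Procedure 3 invites people who used the MVP, not people who completed six months. Because use is individual and renewed monthly, a person stopped at a review may have reached the end of their own deployment. The text permits this reading. If it is intended, one sentence settles the timing, although early stoppers would still not be a sampling characteristic. The topic guide (Multimedia Appendix 3) is not shown and may already ask about stopping.

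The gap in scores is also assumed. Some people will stop for reasons unrelated to usability, and with no gap there is no bias in the mean. Limiting interviews to phase 2 is a defensible choice, since the MVP is the team's own app and the prototype relies on a third-party one.

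A reader might infer more than the documents support:

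- **That nothing is collected from leavers or decliners.** Participants and Recruitment, Outcome 3 and Outcome 5 provide for recording or reporting reasons for nonscreening, nonconsent and leaving, where possible or known.
- **That the rules for declaring a full trial unlikely to be feasible can hardly ever be met.** They do not require data from leavers, and consultation or PPI sessions feed them. Outcomes 1 and 4 also state purely quantitative expectations of 70% and 80%.
- **That the whole usability criterion is biased towards passing.** Its wear-time part is set against 60 participants and is not restricted to completers.
- **That fixed retention counts out of 60 should replace the mixed judgement.** Outcome 1 accepts 70% of the target, 0.70 × 60 = 42 recruits, so a requirement of 48 retained could be impossible to meet. Combining numbers with qualitative judgement is also a legitimate choice in a mixed methods feasibility study.

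**Conclusion.** The point holds for two sources, the MAUQ average and the interview themes. On the natural reading of Procedure 3, together with the monthly engagement condition and a sampling plan that does not mention early stopping, both over-represent participants who stayed. One is a numeric progression criterion and the other informs whether a full trial is feasible.

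The likely size is modest: 0.2 to 0.5 MAUQ points at 80% retention, if leavers would score 1 to 2.5 points below stayers. It matters only when the observed mean is near 5. The estimate rests on the assumed gap, on 80% applying to MVP users at the end of use, and on leavers not being asked. The consultation matter is a gap in stated input, not a failure of the rules. The change is worth making before deployment because it is cheap then and hard to make good afterwards.

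**What to change.** 1. In Procedure 3, offer the MAUQ and the interview invitation to every MVP user at their own stop date, whether that is completion, withdrawal or a monthly-review stop.
2. In Sample Size, add early stopping to the purposive sampling characteristics for the existing 9-12 interviews, and ask early stoppers why they stopped.
3. In Outcome 6, report the MAUQ for early stoppers and completers separately, with the number missing in each group.
4. In the Outcome 3 and Outcome 5 consultations, also seek the views of people who declined or left. State that these views and the recorded reasons inform the judgement that recruitment or retention cannot be improved.

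The cost is small: the number of interviews is unchanged, and the rest is wording, a possible addition to the topic guide and an earlier trigger for the questionnaire. Some stoppers will decline, so the MAUQ will remain incomplete, and its mean is likely to be lower than under end-of-deployment collection.
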